**Methods:**

3000 women nationwide will undergo genetic testing for 19 hereditary cancer genes. This is a randomized four-arm non-inferiority study with equal randomization. The four study arms were selected to independently assess the delivery of genetic information both before and after genetic testing (pre-test and post-test) by either requiring telephone genetic counseling or providing only online education with optional telephone counseling. Patients have post-test telephone counseling when testing positive for a pathogenic inherited mutation in all four arms. Surveys measuring psychological, behavioral and cognitive state are completed online at baseline, 3 months, 12 months and 24 months post-results disclosure. The primary study outcome is cancer-risk distress at 3 months post-result disclosure.

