### Study design

After online eligibility screening and electronic study consent (as approved by the Human Subjects Division of the MD Anderson Institutional Review Board), randomization into one of four study arms is performed automatically using a web-based data management platform [8]. The four study arms were selected to independently assess the delivery of genetic information both before and after genetic testing (pre-test and post-test) by either telephone genetic counseling or online education alone. The control arm requires mandatory pre and post-test telephone counseling while the other three arms provide various combinations (Table 1). Participants are mailed a saliva collection kit after all pre-test online education and/or genetic counseling is completed, based on study arm. Analysis of 19 OC genes is completed once the participant returns the saliva sample. As an additional safety measure, any participant found to carry a pathogenic or likely pathogenic mutation has required post-test telephone counseling and any participant desiring genetic counseling is provided with telephone genetic counseling regardless of study arm. A study schema can be found in Fig. 1. Participants were stratified into one of two risk groups: individuals with a personal and/or family history of cancer, and those with a known familial mutation (cascade group).

**Table 1 Tab1:** Study Arms

	Pre- Genetic Testing	Post- Genetic Testing
Arm A	Online educational video	Online Test Results Report
Arm B	Online educational video	Online Test Results Report + Telephone Genetic Counseling
Arm C (Control)	Online educational video + Telephone Genetic Counseling	Online Test Results Report + Telephone Genetic Counseling
Arm D	Online educational video + Telephone Genetic Counseling	Online Test Results Report

Note: optional telephone genetic counseling is allowed at any point in all arms at patient request and is mandated post-test for all patients with pathogenic mutation regardless of study arm

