### Statistical considerations

We employ a non-inferiority design with a non-inferiority margin of 4 points, as suggested by Schwarz et al. (2014), for the difference in IES score between the control arm and each of the other three study arms at 3 months post-result disclosure.

We are enrolling 5200 eligible women with a goal of 3000 completing genetic testing. We expect that around 85% (*n* = 4400) of those who consent to participate will complete the baseline questionnaire and then be randomized. Of these, we will enroll around 750 subjects with a known familial mutation into the cascade group, with the remaining 3650 subjects, who have an increased likelihood of carrying a deleterious mutation in an ovarian cancer predisposition gene based on personal and family history of disease, as the group of interest for our primary analysis. We expect that 65% (*n* = 2375) of the 3650 participants with personal and/or family history of disease will follow through with providing a saliva sample for analysis, with 75% of those subjects completing the study through the 3 month assessment (*n* = 1780), which equates to about 450 participants on each of the four study arms.

Each of the three experimental study arms will be compared to the control study arm using a one-sided t-test, with the null hypothesis for each of the three tests that the mean stress score in the experimental arm is more than 4 points above the mean stress score in the control arm. A one-sided significance level of 0.025 is targeted across all three tests, resulting in a Bonferroni-corrected significance level of 0.0083 for each test. The sample size was chosen to achieve 93% power for each test, assuming a standard deviation in the scores of 15.3 based on Schwartz et al., yielding an overall power of 80%.

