Our secondary outcome is the “completion rate”, defined as a participant progressing through the entire process from pre-test genetic education/counseling to receiving their test results and post-test genetic education/counseling. We will test two null hypotheses regarding the completion rate: that the completion rate for the participants receiving only online genetic education before testing (Arms A and B) is more than 6% less than it is for participants who were randomized to receive telephone genetic counseling before testing (Arms C and D), and that the completion rate for the participants receiving only online genetic education after testing (Arms A and D) is more than 6% less than it is for participants who were randomized to receive telephone genetic counseling after testing (Arms B and D). This 6% non-inferiority margin is more conservative than the 7.5% margin used by Schwartz et al. [5].

In addition to testing our primary and secondary hypotheses, we will summarize for each study arm the key outcomes related to cognition, affect and behavior, and the changes in scores from baseline. We will also use regression models to model the scores (and changes in the scores from baseline) as a function of study arm, risk group, and other covariates.

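### The second completion-rate hypothesis labels the post-test telephone group Arms B and D, which contradicts Table 1 and the sentence itself; it should read Arms B and C

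*Protocol article*

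**What the plan says.** Under Statistical considerations, the secondary outcome is the completion rate, with two non-inferiority hypotheses, each with a 6-point margin.

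- The first concerns the pre-test step. It sets Arms A and B against "participants who were randomized to receive telephone genetic counseling before testing (Arms C and D".
- The second concerns the post-test step. It sets "participants receiving only online genetic education after testing (Arms A and D" against "participants who were randomized to receive telephone genetic counseling after testing (Arms B and D".

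On the margin, the article says: "This 6% non-inferiority margin is more conservative than the 7.5% margin" of an earlier trial.

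Table 1, under Study design, defines the arms. After testing, Arms A and D receive the online results report alone, and Arms B and C receive the report plus telephone counseling. Arm C is the control, and the text above the table agrees: "The control arm requires mandatory pre and post-test telephone counseling". The abstract describes a "randomized four-arm non-inferiority study with equal randomization".

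**The concern.** The second hypothesis places Arm D on both sides. An arm with no required post-test call is counted as counseled, and the control arm, which does have that call, is left out. The sentence therefore disagrees with Table 1 and with its own first half.

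This is one of only two hypothesis tests stated for the secondary outcome, and it is the article's only definition of the post-test comparison. Someone building the analysis from the printed letters would obtain overlapping groups and a diluted contrast. In a non-inferiority test, dilution favours declaring non-inferiority, here of less counseling. A later reader could also not tell from the text which comparison had been prespecified.

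**Working it through.** **1. Text against Table 1**

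| Arm | Post-test telephone counseling required (Table 1) | Group as printed | Group by Table 1 |
|---|---|---|---|
| A | no | online-only | online-only |
| B | yes | telephone | telephone |
| C (control) | yes | none | telephone |
| D | no | online-only and telephone | online-only |

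The first hypothesis (A and B versus C and D) agrees with the pre-test column of Table 1. Only the last letter of the second is out of line.

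**2. What the printed contrast estimates**

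With equal arms, and letters standing for completion rates:

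- As printed: (A + D)/2 − (B + D)/2 = (A − B)/2. D cancels and C does not appear.
- By Table 1: (A + D)/2 − (B + C)/2 = [(A − B) + (D − C)]/2, the post-test effect averaged over both pre-test conditions.

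The printed contrast reaches −6 points only when A − B = −12 points. Halving is exact for A versus B. It is half the overall post-test effect only if A − B = D − C, that is, with no pre-by-post interaction.

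**3. The plan's own figures**

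No power or sample size is given for completion, so there is nothing to reproduce there. The primary calculation does reproduce. With 450 per arm, SD 15.3, margin 4 and one-sided 0.0083, the SE is 15.3 × √(2/450) = 1.02, and 4/1.02 − 2.395 = 1.53, giving power of 93.7% against the stated 93%. Overall, 0.93³ = 80.4% against the stated 80%.

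**4. Illustration if the printed letters were analysed**

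Inputs from the document:
- margin of 6 points and equal allocation;
- randomized total: "around 85% (*n* = 4400) of those who consent to participate", so 4400/4 = 1100 per arm;
- or, without the cascade group, "with the remaining 3650 subjects, who have an increased likelihood of carrying a deleterious mutation", so 3650/4 = 912.5 per arm.

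Assumptions:
- one-sided alpha 0.025 (stated for the primary tests only);
- completion of 65% in the telephone arms, borrowed from the expected saliva-return rate;
- no interaction and no pre-test effect;
- a true post-test deficit of exactly 6 points, so A = D = 0.59 and B = C = 0.65.

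The printed contrast then centres on 0.59 − 0.62 = −0.03. With n per arm:

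- SE ignoring the overlap: √[(0.59×0.41 + 0.62×0.38)/(2n)] = 0.0147 (n = 1100) or 0.0162 (n = 912.5).
- True SE of (A − B)/2: √[(0.59×0.41 + 0.65×0.35)/(4n)] = 0.0103 or 0.0113.
- P(declare non-inferiority) = Φ[(−0.03 + 0.06 − 1.96 × SE used)/true SE].

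| Test | 1100 per arm | 912.5 per arm |
|---|---|---|
| As printed, SE ignoring overlap | 54% | 44% |
| As printed, SE reflecting overlap | 83% | 75% |
| A and D versus B and C | 2.5% | 2.5% |

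Simulation with 200,000 replicates (912 per arm in the smaller case) gave 54.4% and 43.9% for the first row and 2.5% for the last. At zero true difference, A and D versus B and C has power of 98.7% and 96.7%.

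**5. Sensitivity**

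- Over alpha 0.0125 to 0.05, completion 50% to 90% and both sample sizes, the overlap-ignoring rate runs from 28% to 96%.
- At 80% completion and alpha 0.025, it is 70% (1100 per arm) or 59% (912.5 per arm); reflecting the overlap, 92% or 86%.
- At 65% completion and alpha 0.025, the overlap-ignoring rate falls to 15% to 19% at a true deficit of 8 points, and to about 3% at 10 points.

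**The case against.** The strongest reply is that this is a slip and not a choice of analysis. The comparator is defined in words as those randomized to post-test telephone counseling, and by Table 1 that is B and C. The same sentence puts D in the online-only group, the parallel pre-test hypothesis is right, and the Study design section says the arms were chosen to assess pre-test and post-test delivery independently. All of that stands.

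A reader might infer from the algebra that the trial will run a test that wrongly declares non-inferiority about half the time or more. The documents do not support that. The inflation arises only if the printed letters reach the analysis, and neither an SAP nor analysis code is shown. The rates also rest on inputs the article does not state for this outcome. At one-sided 0.0125, 65% completion and 912.5 per arm, the overlap-ignoring rate is about 29%, so half or more is not robust.

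It can also be said that the harmful scenario is unlikely. Completion includes the post-test step, so a required call is one more hurdle, and the Background itself asks whether required counseling reduces test completion. If online-only completion is equal or better, the intended contrast would very likely reach the same conclusion. That bears on how likely harm is, but the error rate of a non-inferiority test is judged at its margin.

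None of this makes the printed grouping correct.

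**Conclusion.** The group definition is wrong as written. This follows from the document alone and needs no assumption. It is probably a slip for Arms B and C.

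The consequence is conditional. Analysed as printed, the test would drop the control arm and apply a 12-point margin to A versus B, looser than the 7.5% margin the article claims to improve on. Under the stated assumptions, false non-inferiority at a 6-point deficit would be 44% to 54% or 75% to 83%, depending on the standard error, against 2.5% for the intended grouping. These figures illustrate what the label could do; they are not a forecast for the trial.

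The error touches one of two secondary tests. The primary comparison of distress scores is unaffected.

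**What to change.** In Statistical considerations, change the second completion-rate hypothesis to Arms A and D versus Arms B and C, and check that the analysis uses that grouping. This is a one-letter correction with no change to design, sample size or data collection. The article describes the trial as ongoing with no data available; making the correction before analysis avoids any appearance of regrouping after the results are known.

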## Discussion

In-person genetic counseling is likely to remain standard practice in large cancer centers and academic institutions. However, alternative service delivery models for genetic counseling must be further explored to find an optimal balance of clinical quality with increased access and financial sustainability. This is especially important given the largely debated topic of population screening for *BRCA1, BRCA2,* and Lynch syndrome. The discussions surrounding population-based screening for hereditary cancer genes has highlighted a challenge regarding the ability to provide this service on a large scale in an efficient and effective manner [22]. Determining the efficacy of an online genetic SDM may play a vital role in future implementations of population screening.

The nationwide MAGENTA trial is the first study to assess the use of a genetic service model using online access and electronic education for population based testing in individuals at elevated risk of ovarian cancer, while evaluating the need for personal pre and post-test genetic counseling. Innovative service delivery models are essential to decreasing barriers to genetic testing, particularly among underserved populations. Identifying more individuals with inherited cancer susceptibility will allow targeted prevention and ultimately save lives.

## Data Availability

Not applicable. The trial is ongoing and no data is available.

## Abbreviations

IC: Informed consent
MAGENTA: Making genetic testing accessible
OC: Ovarian cancer
SDM: Service delivery model
